## Abstract

**Background:**

Medical progress and the lifestyle modification have prolonged life expectancy, despite the development of chronic diseases. Support and care for older subjects are often provided by a network of informal caregivers composed of family, friends and neighbors, who are essential in helping older persons to continue living at home. It has been shown that the extent and diversity of informal tasks may jeopardize the physical, mental and social wellbeing of caregivers.

**Methods/design:**

The aim of the Informal Carers of Elderly cohort is to define, through a longitudinal study, profiles of caregivers of older patients with a diagnosis of one of the following diseases: cancer (breast, prostate, colorectal), neurodegenerative diseases (Parkinson’s disease, Alzheimer’s disease and similar diseases), neurovascular diseases (stroke), sensory diseases (age-related macular degeneration (AMD)) and heart disease (heart failure). Patients must be at least 60 years old and living in the region of Burgundy-Franche-Comte (France). By following the different phases of the caregiving relationship from the announcement of the diagnosis, it will be possible to assess the quality of life of caregivers, coping strategies, levels of anxiety and depression, social support and the extent of their burden. We will also evaluate the efficacy and efficiency of the implementation of a pragmatic intervention by a social worker to help informal caregivers, through a randomized interventional trial nested in the cohort. Qualitative approaches aimed at studying the caregiver/patient relationship, and situations leading to breakdown of the caregiver relationship will be also undertaken.

**Discussion:**

Through an analytical and longitudinal definition of profiles of informal caregivers, this study will gather detailed information on their life courses and their health trajectory by identifying consequences associated with the concept of their role as carers. In addition, the randomized interventional trial will explore the relevance of the implementation of a supportive intervention by a social worker to help caregivers. These data will help to identify strategies that could be used to improve the existing sources of aid and to propose new approaches to help caregivers. This study will provide the opportunity to identify the most relevant means of support adapted to caregivers, and provide an impulse for new health care policies.

**Trial registration:**

ClinicalTrials.gov Identifier: NCT02626377. Retrospectively registered on 9 December 2015. Protocol date/version: 23 October 2014/version 2.

## Background

In France, almost four million people provide informal care on a daily basis to people aged 60 years and over [1]. The topic of informal caregiving has become a key issue with regard to care and support for, and consequently maintenance at home of, chronically ill older people, and the features and progress of their dependence. Caregivers play an essential role in providing support to patients [1–4]. Different reasons lead people to become caregivers of a patient, such as chronic disease (51 %), older age (44 %), physical handicap (30 %) and mental handicap (13 %) [2]. Among the various diseases, Alzheimer’s disease is the most frequent cause of becoming an informal caregiver (17 %), followed by age-related macular degeneration (AMD) (15 %), heart failure (14 %), hypertension (13 %), cancer (12 %), stroke (10 %), diabetes (9 %), osteoporosis (8 %) and Parkinson’s disease (4 %) [2]. Over the last few years, informal caregivers have been classified as a frail population with an increased risk of health problems themselves. Psychological components of the informal caregiver role, especially chronic stress, are associated with an increased risk of depression, mortality and cardiovascular or neurovascular morbidity [5–7]. The mean duration of informal caregiving situations is about 7 years, and the delivering of care often has deleterious effects on the caregiver’s general health. Forty percent of caregivers believe themselves to be in poor health, although 90 % of caregivers say that they can cope with the difficulties arising from the care relationship. However, they report a deterioration of their family life (35 %), marital life (41 %), mood (49 %), physical condition (57 %) and leisure activities (70 %) [4].

The psychological distress felt by informal caregivers seems to be directly related to the care provided: the time devoted to care and support, the nature of the care, and behavioral disorders. Such distress could be generated by the effects of personal investment in the role of caregiver, namely a reduction in personal leisure time, loss of social links, family conflict and financial difficulties. The care relationship leads to an increase in workload, which is likely to accentuate any latent health problem of the caregiver [8]. The “adjustment” must be made at the cost of time devoted to family, friends or work. Accordingly, 29 % of caregivers think that there is a lack of moral and emotional support [2]. The difficulties experienced by caregivers may, therefore, have a direct impact on the quality of the care provided to patients [9]. It thus seems essential to identify caregivers’ profiles through a longitudinal follow-up of their life course, to study the course of their quality of life, to understand the context in which care is provided, to identify factors that amplify or attenuate “burn-out,” to measure the impact of support on the caregiver’s life, to understand strategies for coping with the stress, and to identify psychological issues. Another important issue is the identification of the most appropriate type of support that could prevent the deterioration of the caregivers’ physical and mental health, and preserve their social environment, thereby ensuring the continuity of therapeutic care to patients. Various forms of support for caregivers are currently available. Previous studies have underlined the efficacy of these interventions for both caregivers and patients [10]. The effects varied according to the age and gender of the caregiver, the social link between caregivers and patients, the duration, the frequency of the “work/care” and the type of intervention. The patient’s disease is also a key component.

To date, few longitudinal studies of caregivers have been conducted. As a result, there is a lack of data to identify caregivers’ profiles in a dynamic construct perspective. Thus, there is a clear need for scientifically validated knowledge of this population. This is a key step in identifying interventional strategies that could be applied and tailored to the caregivers’ profiles. Our hypothesis is that caregivers represent a heterogeneous group of individuals with different needs and different coping strategies. As suggested by previous reports, the support proposed to informal caregivers should be varied and adapted to the individual. In this respect, the Eurofamcare study underlined the need for a systematic evaluation of the role and needs of caregivers [11]. In addition, a meta-analysis showed the importance of screening for burn-out in caregivers on a 6-monthly basis [12]. Other studies have shown how the circumstances in which a person comes to take on the role of caregiver can affect the caregiver-patient relationship. Indeed, in the long term, the relationship devoted to care may be compromised. In this regard, proactive interventions initiated from the earliest stages of the caregiving relationship seem essential in promoting optimized coping [13–18].

These points led us to undertake a longitudinal cohort study to follow the informal main caregivers of patients who are in the early phase of a diagnosis of breast, prostate or colorectal cancer, Alzheimer’s or similar diseases, Parkinson’s disease, stroke, AMD or heart failure.

## Methods/design

### Trial design

This research project is a prospective, multicenter, longitudinal cohort study incorporating two types of study, namely an observational study and a nested randomized interventional trial among caregivers included in the observational study.

#### Observational study

The primary objective of the observational study is to evaluate, using quantitative approaches, the patterns of informal caregivers for patients aged 60 years and older according to the evaluation of their health-related quality of life (HRQoL) (as assessed by the Medical Outcome Study Short Form-36 items (MOS SF-36) and the CareGiver Oncology Quality of Life (CarGOQoL) questionnaires (only for caregivers of the group of cancer patients), coping strategies (as assessed by the coping scale developed by Borteyrou, Truchot and Rascle [35]), anxiety and depression (as assessed by the Hospital Anxiety and Depression Scale (HADS)), social support (as assessed by the Social Support Questionnaire (SSQ6)) and caregiver burden (as assessed by the Zarit Caregiver Burden Interview) during the first 5 years of their role as caregivers.

Using qualitative approaches, the secondary objectives are: (1) to evaluate the caregiver/patient relationship and changes in this relationship over time as the patient’s disease progresses, (2) to describe the specificities of the attachment relationship between a caregiver and a patient with behavioral disorders (Alzheimer-type dementia in particular) and (3) to study the situations leading to a breakdown in the role of caregiver (nursing home placement, death or disease remission) during the 5 years of participation in the cohort duration.

#### Interventional study

A randomized interventional trial in a 1:1 ratio will be conducted within this cohort to evaluate the effect of a pragmatic supportive intervention on caregivers, provided by a social worker and an information booklet (intervention arm) versus the control arm, where caregivers will only receive the information booklet, without social worker support. The intervention will be conducted during the first 2 years of entrance into the caregiver’s role. The intervention proposed here mobilizes social workers of the Departmental Councils, of the General National Retirement Fund (CARSAT Burgundy-Franche-Comté) and of the Community Social Action Association (CCAS of Dijon). All institutions providing social workers are officially involved in the study and all social workers are trained in the management of older people, characteristics of caregiving relationships and in ICE cohort study procedures. The structure and purposes of the social worker’s intervention are described in Table 1. The main objective is to compare the mental and physical health summary scores on the MOS SF-36 at 1 year between the two groups. Secondary objectives are to compare the following parameters between groups: (1) the mental and physical health summary scores of the MOS SF-36 at 2 years, (2) all HRQoL dimensions of the MOS SF-36 at 1 year and at 2 years, (3) longitudinally: all HRQoL dimensions of the MOS SF-36 and the CarGOQoL questionnaire (only for caregivers of the cancer patient group), (4) coping strategies (as assessed by the coping scale developed by Borteyrou, Truchot and Rascle [35]), (5) anxiety-depression (as assessed by the HADS), (6) social support (as assessed by the SSQ6) and the perceived caregiver burden (as assessed by the Zarit Caregiver Burden Interview) and (7) to assess from a societal perspective the incremental cost-effectiveness ratio (ICER) of the intervention of a social worker for caregivers. The ICER will be expressed in terms of quality-adjusted life years (QALYs) gained based on a utility score that will be calculated based on the EuroQoL EQ-5D questionnaire, the SF-6D which is composed of 11 items of the SF-36 questionnaire and the Center for Epidemiologic Studies-Depression Scale (CES-D) questionnaires and economic survey.

**Table 1 Tab1:** Content and purposes of the pragmatic intervention by a social worker in the intervention group of the nested randomized trial for caregivers

Format of the intervention:
For each caregiver randomized to the intervention arm of the trial, a social worker will conduct an individual interview with the caregiver
Purposes of the interview:
To simply listen to the caregiver and allow them to express their complaints (and to be attentive to unspoken complaints) To evaluate the level of difficulty experienced by the caregiver in their daily routine, being attentive to their personal situation To respect and respond to any needs and/or requests expressed by the caregiver, and provide active support; guarantee confidentiality of the conversations and ensure that the caregiver participates willingly, without intruding in their life To provide any resources that are lacking in the caregiver-patient relationship; provide information about available solutions for respite care, and other solutions specific to each case (accommodation, health care pathway, logistic/material support for the caregiver/patient) To help the caregiver to more quickly apprehend and come to terms with their commitment of being a caregiver To be attentive to any alert signals and prevent deterioration towards crisis situations (burn-out, abuse); to alert third parties if the caregiver is found to be in a critical situation Through their interactions with the caregiver, the social worker will provide accompaniment and support, offering pertinent information and orientation towards appropriate structures of care depending on the situation the caregiver describes. The intervention leaves it to the discretion of the social worker to decide what is the most appropriate way to operate and the most appropriate solution to propose in practice for each caregiver The intervention also aims to determine whether the needs expressed by the caregivers vary according to the patient’s disease, or according to the patient’s age, sex or place of residence. After the intervention, the social worker will complete a standardized Data Transmission Sheet, with the Linear Analogue Scale Assessment quality of life (LASA) questionnaire (about the caregiver but completed by the social worker), to be forwarded to the study coordinator. They will receive receipt of their submission once the forms have been submitted

The duration of patients’ and caregivers’ participation in the cohort study is 5 years. The entire cohort study’s duration is 10 years: 5 years of inclusions and 5 years of follow-up. Only the interventional study is restricted to 2 years.

The logistic support of the study will be carried out by three clinical research assistants (CRAs) (one in each center) who are involved in the ICE cohort project and who have also participated in the reflection phase during the writing of the study protocol. They will be in charge of patient screening, questionnaire sending, data collection and for following patients/caregivers.

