With a bilateral alpha risk of 5 % and a statistical power of 90 % to detect a difference of at least 5 points (standard deviation (SD) = 25), and adjusted to take account of the number of statistical tests and maintain an overall alpha type one error rate of 5 % (Bonferroni adjustment):With two dimensions of HRQoL, α’ = α/2 = 0.05/2 = 0.025With five groups of diseases, α” = α’/5 = 0.025/5 = 0.005 (cancer (breast, prostate, colorectal); neurodegenerative disease (Alzheimer’s disease and similar diseases); AMD; neurovascular (stroke); cardiac (heart failure))At least 1684 caregivers should be randomized in each disease group. However, we anticipate lower recruitment in the heart failure group. Accordingly, only 488 caregivers will be randomized (bilateral α type I error of 0.005 and statistical power of 80 %) to demonstrate a difference of at least 5 points (SD = 15). Thus, it will be necessary to include and to randomize 4 × 1684 = 6736 caregivers, plus 488 in the heart failure group, representing a total of 7224 caregivers. An interim analysis will be planned to reject either H0 or H1 (Alpha Spending Function and O’Brien-Fleming Boundaries) when half the caregivers have been included with 1 year of follow-up in each of the subgroups. To allow for 5 % of loss to follow-up, it will be necessary to include and randomize an additional 380 caregivers, resulting in an overall total of 7604 caregivers (1750 caregivers for each of the four large groups of diseases and 604 for the heart failure group)

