#### Analysis

Analyses will be performed using SAS (version 9.4) (SAS Institute Inc., Cary, NC, USA), R (version 3.2.2) [49] and Stata (v13) (StataCorp LP, TX, USA) software. The statistical analysis plan for the primary and secondary objectives will be written before the database is locked.

All analyses will be on a modified intention-to-treat principle, i.e., including all randomized informal carers regardless of the eligibility criteria and intervention received, with MOS SF-36 scores available at baseline and 1 year. Analyses for the interventional study will be done on an intention-to-treat basis. After Bonferroni adjustment, statistical significance will be fixed at the 0.005 level for primary analyses, and at the 0.05 level for the secondary objectives.

An interim analysis is planned when half of the patients will be included to reject or not H0 (efficacy) or H1 (futility); the Alpha Spending Function with O’Brien-Fleming Boundaries will be used to determine the alpha-level significance at the interim and at the final analysis using EAST® software (Cytel Software Corporation, Cambridge, MA, USA) [50]. The corresponding confidence interval will be computed (1 − alpha level).

Sociodemographic and clinical characteristics will be described at inclusion using frequency (percent) for qualitative variables and mean (SD), or median (min–max) for continuous variables. Data will be compared between randomization arms using the Student *t* test or the nonparametric Mann-Whitney test, or analysis of variance (ANOVA) or the Kruskal-Wallis test for continuous variables and the Chi-squared or Fisher’s exact tests for qualitative variables, as appropriate. Scores will be described at each follow-up time point using mean (SD) and median (min–max) in each arm.

After describing missing data and investigating the mechanism of missing data profiles, imputation will be performed using a multiple imputation method by sensitivity analysis after checking normality, and univariate and multivariate ANOVA adjusted for baseline score will be performed to compare the two summary scores of the SF-36 questionnaire at 1 and 2 years.

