Multivariate analyses will be performed including at least the stratification criteria for randomization, as well as variables associated with HRQoL at the 10 % level by univariate analysis. HRQoL data will also be longitudinally analyzed using a mixed model of analysis of variance for repeated measures (or pattern mixture models in case of a missing-not-at-random profile) in order to test an arm effect, time effect and an interaction between arm and time, as well as the effect of other relevant parameters (HADS, coping, clinical parameters, etc.). Some random effects on patients will also be introduced into the model in order to reflect individual trends. Burden, coping and HADS will also be modeled as time-dependent covariables in another model. Time to HRQoL score deterioration will be estimated using the definitions of both Bonnetain et al. [51] and Hamidou et al [52]. Item Response Theory, cluster analyses, structural equation modeling as well as classical factorial analyses will be conducted as complementary analyses to define and validate longitudinal profiles of caregivers. All these analyses will be repeated in each subgroup defined by stratification (including cancer localizations) for sensitivity analyses.

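### Social workers treat only the intervention arm, but neither the sample size nor the named models allow for correlation between caregivers who share a worker

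*Protocol article*

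**What the plan says.** Caregivers are randomized individually, 1:1 within each disease group. In the intervention arm a social worker holds one-hour individual interviews every 6 months from month 6 to month 24 (Randomization procedure). Table 1 states that "The intervention leaves it to the discretion of the social worker to decide what is the most appropriate way to operate", and extends that discretion to the solution proposed for each caregiver. The control arm gets the information booklet only, although controls may approach social services themselves.

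For the large groups, the Sample size calculation section concludes: "At least 1684 caregivers should be randomized in each disease group". This rests on a 5-point difference, SD 25, 90% power and a two-sided level of 0.005. For heart failure, "only 488 caregivers will be randomized", with SD 15 and 80% power. The only adjustments described are the Bonferroni correction and 5% loss to follow-up.

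The Analysis section says "statistical significance will be fixed at the 0.005 level for primary analyses". For the primary comparison, "univariate and multivariate ANOVA adjusted for baseline score will be performed to compare the two summary scores of the SF-36 questionnaire". Multivariate models include at least the stratification factors, which include center. For the longitudinal model, "Some random effects on patients will also be introduced into the model in order to reflect individual trends". No section mentions a social-worker effect, an ICC, a design effect or a cluster-robust variance. The Discussion deals with homogeneity between workers by training and a partnership agreement.

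**The concern.** This is a partially nested design: caregivers in one arm are grouped by the person who delivers the intervention, and caregivers in the other arm are not. If some workers are more effective than others, caregivers of the same worker have correlated outcomes, and the variance of the intervention-arm mean is larger than a formula for independent observations gives. The standard error of the arm difference is then too small.

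Two things follow. A test run at a nominal 0.005 rejects more often than that when the average effect is zero but workers differ. Power at a true 0.005 level is below the calculated figure. The strict threshold sharpens the first effect, because a small error in the standard error has a larger relative effect far out in the tail. Adjusting for center removes variation between centers, but not variation between workers within a center.

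**Working it through.** **Inputs from the protocol article.** Two-sided level 0.005 per test (0.05 / 2 summary scores / 5 disease groups). Large groups: difference 5, SD 25, 842 per arm (1684 / 2). Heart failure: difference 5, SD 15, 244 per arm (488 / 2).

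**Assumptions.** The ICC for social workers and the number m of intervention caregivers per worker *within one disease group* are not in the document. I take ICC 0.01 to 0.05 and m from 2 to 20. The relevant m is per disease group, because each primary test is run within one group.

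**Step 1: reproduce the stated sizes.** Per arm, n = 2(z₁ + z₂)² SD² / 5², with z₁ = 2.807.
- Large groups: 2(2.807 + 1.282)² × 625 / 25 gives 836 per arm, 1672 in total (stated 1684).
- Heart failure: 2(2.807 + 0.842)² × 225 / 25 gives 240 per arm, 480 in total (stated 488).

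The stated numbers agree with the plain two-sample formula to within 3%. With 842 and 244 per arm, power under independence is 90.3% and 80.9%, so there is almost no room for a design effect.

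**Step 2: allow for clustering in one arm.**
- Intervention-arm design effect: DE = 1 + (m − 1) × ICC; control arm unchanged.
- SE = SD × √[(1 + DE) / n per arm].
- True level of the unadjusted test: 2 × [1 − Φ(2.807 × √(2 / (1 + DE)))].
- Power at a valid 0.005 level: Φ(5 / SE − 2.807).

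Example, large group, ICC 0.05, m = 10: DE = 1.45; SE = 25 × √(2.45 / 842) = 1.349; true level = 2 × [1 − Φ(2.536)] = 0.011; power = Φ(5 / 1.349 − 2.807) = 81.6%.

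| m per group | ICC | DE | True level | Power, large group | Power, heart failure |
|---|---|---|---|---|---|
| 2 | 0.01 | 1.01 | 0.0051 | 90.1% | 80.7% |
| 2 | 0.05 | 1.05 | 0.0056 | 89.4% | 79.7% |
| 5 | 0.01 | 1.04 | 0.0054 | 89.5% | 79.9% |
| 5 | 0.05 | 1.20 | 0.0074 | 86.6% | 75.9% |
| 10 | 0.01 | 1.09 | 0.0060 | 88.6% | 78.7% |
| 10 | 0.05 | 1.45 | 0.0112 | 81.6% | 69.8% |
| 20 | 0.01 | 1.19 | 0.0073 | 86.7% | 76.2% |
| 20 | 0.05 | 1.95 | 0.0208 | 71.6% | 58.9% |

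**Step 3: familywise error.** Over ten tests taken as independent, 1 − (1 − level)¹⁰ is about 5% to 7% for m of 2 to 5, and reaches 10.7% at m = 10 with ICC 0.05. Independence is an approximation, since the two summary scores come from the same caregivers.

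**Step 4: what each m implies.** The intervention arms hold 4 × 842 + 244 = 3612 caregivers. If every worker served all disease groups, m = 20 in a large group would mean about 842 / 20 = 42 workers with 3612 / 42 = 86 caregivers each. On the same basis, m = 10 means about 84 workers with 43 each, and m = 5 about 168 workers with 21 or 22 each. With 42 workers, heart failure would have only 244 / 42, or about 6, per worker, so the heart-failure figures at m = 20 are more extreme still.

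**The case against.** The strongest objection concerns size. A reader might infer that each worker sees many caregivers, but the article does not say so. The Discussion speaks of training all registered social workers in the region, and several institutions supply them, which points to a broad pool and a small m. The ICC may also be low: the interview is standardized and semidirective, discretion includes tailoring to each caregiver (which adds variation within workers too), and at most two visits, at months 6 and 12, fall by the 1-year endpoint. If workers have no effect at all, the ICC is zero. All of this stands and moves the likely effect towards the low end of the table.

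A reader might also infer that real power is below 90%. That is not established, because the sample size takes no credit for the planned baseline adjustment. Assuming a baseline correlation of 0.5, the SD becomes 25 × √0.75 = 21.65. With ICC 0.05 on that adjusted scale and m = 10, SE = 21.65 × √(2.45 / 842) = 1.168 and power is about 93%. The choice of SD also matters more than clustering: with the heart-failure SD of 15, a large group at ICC 0.05 and m = 20 keeps about 99.8% power. Neither point corrects the type I error.

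Finally, one could say that this is a detail for the statistical analysis plan. In part that is fair: the article never states that errors are independent, says random effects on patients without saying only, and leaves the covariate list open. It should not be read as ruling out a worker term. But the sample size is fixed here and reproduces only under independence, and the models are named here without that level.

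**Conclusion.** The point holds in a limited form. The direction follows whenever workers differ and m exceeds 1: the unadjusted 0.005 tests are liberal, and the 90% and 80% power, as calculated without baseline adjustment, are too high. The size depends on two quantities the document does not give. At the more plausible 2 to 5 caregivers per worker per disease group, with ICC 0.01 to 0.05, the effect is mild. At 10 per worker it becomes material, with the true level up to about twice nominal. Twenty per worker is an upper extreme (level 0.007 to 0.021, power 87% to 72% in a large group). The familywise figure of about 19% that follows from its worst case (1 − 0.9792¹⁰) should not be read as the expected result, least of all because it applies m = 20 to heart failure as well. The reason to act is that the correction is cheap and worker identity may be hard to recover if it is not recorded during delivery.

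**What to change.** - Make sure the Data Transmission Sheet, which the social worker already completes after the intervention, records a social-worker identifier. The text does not say that it does.
- In the primary baseline-adjusted model and the repeated-measures model, add a social-worker random effect in the intervention arm only, or use a cluster-robust variance. Treat each control, and each intervention caregiver never seen by a worker, as their own cluster.
- Set in advance a rule for caregivers seen by more than one worker, such as the first worker assigned. The article does not say that the same worker returns, so simple nesting cannot be taken for granted.
- Report the estimated ICC, and restate the 90% and 80% power over a stated range of ICC and of caseload per disease group, saying whether baseline adjustment is counted.

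The cost is one identifier field, one model term, slightly wider intervals and a slightly less favourable stated power. If the ICC proves close to zero, little is lost.
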